## Methods/design

### Trial design

This is a multicenter, prospective, randomized controlled trial supported by the Shanghai Science and Technology Commission. The trial will be carried out jointly by the Seventh People’s Hospital affiliated to Shanghai University of Traditional Chinese Medicine and two other hospitals in Shanghai. Patients meeting the pre-defined criteria will be randomly divided into three groups: an acupuncture group undergoing fascial-point acupuncture with routine rehabilitation treatment, a sham acupuncture group undergoing sham acupuncture near the fascial point with routine rehabilitation treatment, and a control group undergoing routine rehabilitation treatment. The patients will be followed up for 6 months to observe their hand spasm and limb function after treatment. The study flow chart is shown in Fig. 1. An example template for the content of admission plans, interventions and evaluation recommendations is shown in Fig. 2.

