### Randomization

After signing the informed consent, participants will be randomly divided into three groups: an acupuncture group, a sham acupuncture group and a control group. Randomization will be accomplished by qualified researchers using randomization software to generate random-number sequences. In the process of randomization, allocation should be kept hidden. All patients will be randomly divided into groups in a ratio of 1:1:1. The strips revealing treatment allocation will be placed in sealed opaque envelopes with sequential numbers. After obtaining informed consent, the envelopes will be opened in turn. Patients and data analysts are not clear about the randomized grouping.

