### Intervention

The interventions in the three groups are as follows:
Acupuncture group

In addition to routine rehabilitation treatment, fascial-point acupuncture will be given five times a week for 4 weeks, with 30 min each time.

Location of fascial points: the patient will be in a sitting or supine position and the physician will be placed on the affected side. First, 75% alcohol cotton ball will be used to disinfect the patients´ dorsal between the first metacarpal bone and the second metacarpal bone and the thumb of the operator. Then, the operator will apply one-way pressure with thumb on the dorsal between the first metacarpal bone and the second metacarpal bone from the distal end to the closel end. During this process, the most obvious pain point or a cord nodule can be touched can be touched, which is the fascial point as shown in Fig. 3.

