**Fig. 3 Fig3:**
[figure not shown]
Location of fascial points

Acupuncture method: routine disinfection will be carried out on the hand of the operator and the relevant fascial point of the patient. According to individual differences of patients, different specifications and models of needles will be selected (25 mm–40 mm). Physicians quickly penetrate skin through the epidermis into the subcutaneous tissues about 1–2.5 cm with the needle tip vertical using a single-handed or two-handed needle-insertion method, and then through lifting, inserting and twisting, aim to enhance the needling sensation. The physician will stop manipulating the needle when there is a sense of needle ‘stagnation, described as being like “a fish swallowing a hook.” At the same time, pain and numbness will appear in the fascia area of the patient, and conduct to the fingers, resulting in tremor and convulsion of the hand.Pressing the needle hole with a dry, cotton-wool ball after needle removal is done to prevent bleeding. In the process of the needling operation, attention should be paid to coordinating the operation of both hands so as to achieve accuracy, rapidity of treatment, and painlessness or minimal pain.
2.Sham acupuncture group

In addition to routine rehabilitation treatment, treatment using false acupuncture beside the fascial points will be given five times a week for 4 weeks, with 30 min each time.
3.Control group

Routine rehabilitation treatment will be given five times a week for 4 weeks. Conventional rehabilitation treatment mainly includes:
Good limb position: the affected upper limb maintains the position of abduction, external rotation, elbow extension, forearm supination, wrist and finger extensionBobath’s handshake exercises: the arm is raised over the head, and the mind is used to force the limbs on both sides 10 times a time for six times a dayExercise therapy: continuous stretching of spastic muscles and joint-loosening if necessary. The induced segregation movement and other manipulations are performed after relaxation of the spastic muscle, 45 min each time once a day

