### Outcome measures

Therapeutic evaluation will be carried out by the same team member who will be blinded to treatment allocation. The primary evaluation indicators in this study are the hand-spasm score and the duration of spasm relief. The modified Ashworth scale will be used to evaluate the spasm of the hand (mainly including the thumb and the other four fingers) before and after treatment. After the patients have been treated with acupuncture and spasticity relieved, the timing will be started to evaluate the duration of spasticity relieved (during this period, the patient should avoid mental tension, so as not to interfere with the test results).

The secondary evaluation indicators included using electromyography (EMG) to detect the activity of the affected limbs, limb function and activity of daily living evaluation. The modified Ashworth scale will be used to evaluate the degree of hand spasm on the affected side at baseline, 4 weeks after intervention and at 1, 2, 4 and 6 months of follow-up [22]. The modified Ashworth scale was divided into 0, 1, 1^+^, 2, 3 and 4 grades, and was quantified as 0, 1, 2, 3, and 4 and 5 points, respectively (Table 1). Surface EMG will be used to record the changes in surface EMG of the upper limbs on the affected side at baseline and 4 weeks after intervention [23]. The simplified Fugl-Meyer scale will be used to evaluate the upper-limb motor function on the affected side and the modified Barthel Index will be used to evaluate activities of daily living at baseline, 4 weeks after intervention and at 1, 2, 4 and 6 months of follow-up [24, 25]. All measurements will be recorded in the data center.

**Table 1 Tab1:** Modified Ashworth scale

Grade	Assessment standard	Score
0	No increase in muscle tension	0
1	Muscle tension is increased slightly. When the affected part is passively flexed and stretched, it suddenly becomes stuck at the end of joint activity and then presents minimum resistance or release	1
1^+^	Muscle tension is increased slightly. Suddenly stuck in passive flexion and extension occurs within the last 50% of the range of ROM, and then shows minimal resistance	2
2	Muscle tension is increased significantly. Muscle tension of the affected limbs in passive motion increases significantly in most ROM ranges, but still easy to move	3
3	Muscle tension is increased severely. The affected limb’s passive movement has resistance over the whole ROM, so it is difficult to move	4

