## Discussion

The timely relief of spasticity in stroke patients is particularly important for the rehabilitation of limb function, so it is a key step to apply effective treatment measures to relieve spasticity as much as possible. A preliminary clinical observation of 16 cases of hand spasm after stroke treated by fascial-point acupuncture has been completed in our group. The results show that fascial-point acupuncture can effectively alleviate hand spasm immediately after stroke. However, its cumulative effect, duration of spasm relief and long-term efficacy need further clinical study. Hence, here we propose a multicenter, prospective and randomized clinical trial to further evaluate the clinical efficacy of fascial-point acupuncture in relieving hand spasm after stroke.

In order to eliminate the interference of acupuncture itself on the experimental results, a sham acupuncture group will be established in this study. However, bias exists in all clinical trials. In our trial, the blindness of the acupuncturists and patients in designing a randomized controlled trial involving acupuncture manipulation will be the most challenging aspect. Therefore, surface EMG measurements are also used as part of the outcome assessment in addition to the scales used in previous studies. In recent years, EMG has been widely used in spasticity assessment, especially after stroke [26]. The application of electrophysiological measurement can provide quantitative information of spasticity and reduce the interference of subjective factors in scale evaluation. In addition, the multicenter development of the study is also related to biases, mainly including differences in acupuncture techniques. We tried to eliminate these biases by examining the needling procedures of other participating hospitals and training acupuncturists in all participating centers. We firmly believe that the results of this study will help to lay a foundation for the alleviation of hand spasm after stroke and functional improvement.

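### Patient blinding is claimed without exception, but it can hold at most between real and sham acupuncture; both comparisons with the control arm are patient-unblinded, though assessor-blinded

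*Protocol article*

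**What the plan says.** The Randomization section describes three arms: "All patients will be randomly divided into groups in a ratio of 1:1:1". On blinding it says: "Patients and data analysts are not clear about the randomized grouping". No arm is excepted.

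The treatments are as follows.

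- **Acupuncture** (Intervention): on top of routine rehabilitation, "fascial-point acupuncture will be given five times a week for 4 weeks, with 30 min each time".
- **Sham** (Intervention): on top of routine rehabilitation, "treatment using false acupuncture beside the fascial points will be given five times a week for 4 weeks, with 30 min each time".
- **Control** (Intervention): "Routine rehabilitation treatment will be given five times a week for 4 weeks". The Trial design section agrees: "a control group undergoing routine rehabilitation treatment". The listed components are positioning, handshake exercises and exercise therapy; none involves a needle.

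On assessment, the Outcome measures section says: "Therapeutic evaluation will be carried out by the same team member who will be blinded to treatment allocation". The Discussion gives the reason for the sham arm, which is to remove the influence of acupuncture as such on the results. It also concedes that "the blindness of the acupuncturists and patients in designing a randomized controlled trial involving acupuncture manipulation will be the most challenging aspect".

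**The concern.** The blinding sentence claims something that the three arms do not allow. A patient who is never needled cannot be unaware of that.

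This matters for interpretation. The outcomes include hand tone on passive movement, a motor scale that needs the patient's effort, daily-living scores and the duration of spasm relief. Some of these can plausibly respond to expectation and co-operation. The Outcome measures section itself asks patients to avoid mental tension while relief is being timed, because tension could disturb the result. A blinded assessor protects against biased rating. It does not remove a difference that arises in the patient, because the assessor will record that difference faithfully.

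If a favourable acupuncture-versus-control result were reported under the present blinding sentence, a reader could credit fascial-point needling with a difference that any needling, or the expectation attached to it, might have produced.

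**Working it through.** The plan gives no figure on this point, so the main check sets the sections side by side.

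**Step 1: who can be blind to what.** Each needled arm has 5 sessions a week × 4 weeks = 20 needling sessions. The control arm has none.

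| Contrast | Patient blinding possible? | Assessor stated blinded? | What the difference contains |
|---|---|---|---|
| Acupuncture v sham | Yes, if the sham is credible | Yes | Effect of needling the fascial point |
| Acupuncture v control | No | Yes | Fascial-point effect plus non-specific needling and expectation effects |
| Sham v control | No | Yes | Non-specific needling and expectation effects only |

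Three arms give three pairwise contrasts, and two of them include the un-needled arm. At 1:1:1, 210 / 3 = 70 patients are controls.

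**Step 2: does another section limit the claim?** The Discussion calls the blinding of acupuncturists and patients difficult, but it does not confine the Randomization statement to the two needled arms. The statement stands uncorrected.

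**Step 3: illustration of the attribution problem.** These inputs are partly assumed.

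- n = 63 per arm, from the Sample size section.
- Two-sided 5% test, from the Statistical analysis section.
- Control relief rate p0 = 50%: an assumption. The article uses 50% for conventional acupuncture, which is none of the three arms.
- Non-specific gain d of 5 to 20 points with needling and no fascial-point effect: an assumption without a source in the documents.

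With p1 = p0 + d and p̄ = (p0 + p1)/2, the probability of a significant result in favour of acupuncture is approximately

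Φ( [d − 1.96·√(2p̄(1−p̄)/n)] / √([p0(1−p0) + p1(1−p1)]/n) ).

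For d = 0.10:

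- p̄ = 0.55, and √(2 × 0.55 × 0.45 / 63) = 0.0886
- √((0.25 + 0.24)/63) = 0.0882
- (0.10 − 1.96 × 0.0886)/0.0882 = −0.84, and Φ(−0.84) ≈ 0.20

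| Assumed non-specific gain | Chance that acupuncture v control is significant |
|---|---|
| 5 points | about 8% (9% if the opposite tail is counted) |
| 10 points | about 20% |
| 15 points | about 40% |
| 20 points | about 63% |

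Under these assumptions acupuncture and sham have the same relief rate, so acupuncture versus sham keeps its 5% level.

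**The case against.** The strongest reply has four parts.

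**The trial is not open-label.** A reader might infer from the missing patient blinding that two of the three comparisons are open-label. The documents do not support that: the outcome assessor and the data analysts are both stated to be blinded, and the modified Ashworth grade is given by the assessor. The accurate description is patient-unblinded and assessor-blinded. This part stands in full.

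**The sham arm already does the isolating.** The Discussion gives it that task, and the contrast exists in the design. A comparison with routine care is legitimate in its own right. This also stands. The contrasts with control are not faulty for failing to isolate the fascial point; they only need to be described as what they are.

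**Nobody says that the claim will rest on the control arm, and the ranking of contrasts may stand in a fuller document.** That is fair, and the absence of a ranking from a condensed article is not charged as an error here. The blinding sentence is another matter: it is stated, and no analysis plan can make it true.

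**The figures are assumed, and the test is not at fault.** A reader might take the 20% as an inflated type I error. It is not. If relief truly differs by 10 points between acupuncture plus rehabilitation and rehabilitation alone, the null hypothesis of that comparison is false and the test has found a real difference. The mistake would lie in attributing it to the fascial point.

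The Discussion also names surface electromyography as a response to the blinding difficulty. That may reduce subjectivity in rating, but it is a secondary measure and does not make control patients blind.

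**Conclusion.** The point holds, within limits. The Randomization section states patient blinding without exception. The design can offer it in at most one of three pairwise contrasts, and the 70 control patients cannot have it. This follows from the treatment descriptions alone and needs no assumption.

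It also follows that acupuncture versus control cannot by itself support a conclusion on the specific efficacy of fascial-point acupuncture. How large the misattribution could be is unknown. The range of about 8% to 63% depends wholly on the assumed non-specific gain of 5 to 20 points and the assumed 50% control rate.

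Nor should it be inferred that blinding between acupuncture and sham is assured, or that it fails. The Intervention section describes conducted pain and numbness, with tremor and convulsion of the hand, for real needling, and describes no matching reaction for sham. The documents therefore support blinding there as an intention and leave its success open.

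**What to change.** Reword the blinding sentence in the Randomization section along these lines:

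> Patients are intended to be blinded only between the acupuncture and sham arms; control patients are not blinded; the outcome assessor and data analysts are blinded to allocation.

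Then state in the protocol or analysis plan that:

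- acupuncture versus sham carries the conclusion on the specific efficacy of fascial-point acupuncture, in line with the Discussion's reason for the sham arm;
- acupuncture versus control is reported as a patient-unblinded, assessor-blinded comparison of the added treatment package with routine care, and cannot alone support that conclusion.

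If expectation-effect figures are shown anywhere, label them as illustrative assumptions about attribution.

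The cost is wording only, with no change to arms, treatment, sample size or recruitment. The downside is that the efficacy claim then rests on the contrast likely to show the smaller difference.

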### Intervention

The interventions in the three groups are as follows:
Acupuncture group

In addition to routine rehabilitation treatment, fascial-point acupuncture will be given five times a week for 4 weeks, with 30 min each time.

Location of fascial points: the patient will be in a sitting or supine position and the physician will be placed on the affected side. First, 75% alcohol cotton ball will be used to disinfect the patients´ dorsal between the first metacarpal bone and the second metacarpal bone and the thumb of the operator. Then, the operator will apply one-way pressure with thumb on the dorsal between the first metacarpal bone and the second metacarpal bone from the distal end to the closel end. During this process, the most obvious pain point or a cord nodule can be touched can be touched, which is the fascial point as shown in Fig. 3.

**Fig. 3 Fig3:**
[figure not shown]
Location of fascial points

Acupuncture method: routine disinfection will be carried out on the hand of the operator and the relevant fascial point of the patient. According to individual differences of patients, different specifications and models of needles will be selected (25 mm–40 mm). Physicians quickly penetrate skin through the epidermis into the subcutaneous tissues about 1–2.5 cm with the needle tip vertical using a single-handed or two-handed needle-insertion method, and then through lifting, inserting and twisting, aim to enhance the needling sensation. The physician will stop manipulating the needle when there is a sense of needle ‘stagnation, described as being like “a fish swallowing a hook.” At the same time, pain and numbness will appear in the fascia area of the patient, and conduct to the fingers, resulting in tremor and convulsion of the hand.Pressing the needle hole with a dry, cotton-wool ball after needle removal is done to prevent bleeding. In the process of the needling operation, attention should be paid to coordinating the operation of both hands so as to achieve accuracy, rapidity of treatment, and painlessness or minimal pain.
2.Sham acupuncture group

In addition to routine rehabilitation treatment, treatment using false acupuncture beside the fascial points will be given five times a week for 4 weeks, with 30 min each time.
3.Control group

Routine rehabilitation treatment will be given five times a week for 4 weeks. Conventional rehabilitation treatment mainly includes:
Good limb position: the affected upper limb maintains the position of abduction, external rotation, elbow extension, forearm supination, wrist and finger extensionBobath’s handshake exercises: the arm is raised over the head, and the mind is used to force the limbs on both sides 10 times a time for six times a dayExercise therapy: continuous stretching of spastic muscles and joint-loosening if necessary. The induced segregation movement and other manipulations are performed after relaxation of the spastic muscle, 45 min each time once a day

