### Recruitment

Recruitment of patients began on 1 June 2019 and will be completed in June 2021, or after the required number is obtained, whichever is earlier. We will develop plans and methods to contact subjects, including the preparation of informed consent, obtaining necessary data, videos and pictures to help subjects understand the purpose and program of the trial. We will also explain to the subjects the advantages and disadvantages of the treatment and the relevant safety measures to be taken during the trial. In addition, we will post recruitment posters in and around the hospital, or use the Internet for recruitment. According to the inclusion/exclusion criteria, the research team will preliminarily judge the possibility of each subject’s inclusion, and conduct the relevant examination on them after they have signed the informed consent, and finally confirm whether the subjects actually meet the inclusion/exclusion criteria according to the examination results.

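### The unqualified claim that patients do not know their group is not supported by the real and sham needling as described, nor by a control arm without needles

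*Protocol article*

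**What the plan says.** **Claims.** The Randomization section says, with no arm excepted, "Patients and data analysts are not clear about the randomized grouping". The Outcome measures section adds "Therapeutic evaluation will be carried out by the same team member who will be blinded to treatment allocation".

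**Real needling** (Intervention, acupuncture method). The operator is to work the needle: "through lifting, inserting and twisting, aim to enhance the needling sensation". Then "The physician will stop manipulating the needle when there is a sense of needle" stagnation, which is something the operator feels. At that moment "pain and numbness will appear in the fascia area of the patient, and conduct to the fingers, resulting in tremor and convulsion" of the hand.

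**Sham needling** (Intervention). One sentence: "treatment using false acupuncture beside the fascial points will be given five times a week for 4 weeks", 30 minutes each time, on top of routine rehabilitation. Device, penetration, manipulation and expected sensation are not given.

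**Control arm** (Trial design; Intervention). Routine rehabilitation only, without needling of any kind.

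**Acknowledgement and remedy** (Discussion). The article concedes that keeping acupuncturists and patients blind is its hardest problem, and gives this as the reason for adding surface EMG. Under Outcome measures, EMG is secondary and recorded at baseline and 4 weeks. The primary measures are the hand-spasm score and the duration of spasm relief.

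**The concern.** The Discussion gives the sham arm one purpose: to separate the effect of the fascial point from the effect of being needled. Only the acupuncture-versus-sham contrast can do this, and for patients it is the only contrast that could be blind. If real needling produces a response that the patient feels and sees, and sham needling does not, patients may work out their arm early in the 20 sessions (5 per week for 4 weeks).

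This matters because both primary measures depend on muscle tone. The Outcome measures section tells patients to avoid mental tension while relief is timed, because it would disturb the result. The protocol therefore recognises a route from the patient's state of mind to a primary outcome. Expectation and relaxation in patients who recognise real needling would travel that route, and a blinded assessor would record the result faithfully without being able to remove it.

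**Working it through.** **1. The claim against the description.** The plan has no figure of its own on blinding, so the first step compares passages.

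| Group | What the patient can perceive, as described | Does the text support the claim that patients do not know their group? |
|---|---|---|
| Acupuncture | Manipulation to strengthen sensation; pain and numbness running to the fingers; tremor and convulsion of the hand | Doubtful |
| Sham | Needling nearby on the same schedule; response not described | Cannot be judged |
| Control | No needling | No: these patients can tell they are in neither needling arm |

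**2. What each safeguard covers.**
- Blinded assessor and analysts: these limit bias in scoring and analysis for all three contrasts. They do not affect what the patient knows.
- Sham on the same schedule, near the same point: this helps patient blinding in part.
- Surface EMG: this reduces subjectivity in scale scoring. It does not keep a patient unaware, and it is neither of the two primary measures.

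**3. Illustration of size.** The documents give no estimate of the bias, so the shift d is an assumption. The 63 per arm is the Sample size section's stated number before the 10% allowance, taken as given. The test is two-sided at 5%, as in Statistical analysis, and there is no true effect.

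SE of a standardised difference = √(2/63) = 0.178 SD.

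False-positive rate = 1 − Φ(1.96 − d/SE) + Φ(−1.96 − d/SE).

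| Assumed d (SD) | d/SE | False-positive rate |
|---|---|---|
| 0 | 0 | 5% |
| 0.1 | 0.56 | 8.7% |
| 0.2 | 1.12 | 20% |
| 0.3 | 1.68 | 39% |

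The trial is sized on a binary outcome (relieved or not), so the same check was made on that scale: 50% response in both arms, 63 per arm, and recorded response in the real arm raised by b. The rejection rate uses SE₀ = √(2p̄(1−p̄)/63) for the critical value and SE₁ = √[(p₀(1−p₀) + p₁(1−p₁))/63] for the spread. For b = 10 points, SE₀ = 0.0886 and SE₁ = 0.0882. The upper tail is 1 − Φ[(1.96 × 0.0886 − 0.10)/0.0882] = 1 − Φ(0.84), which gives about 20%. For b = 5, 10 and 15 points the rates are about 9%, 20% and 40%.

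**4. What one guess question can show.** With n patients in an arm and proportions c guessing correctly and i incorrectly, the Bang index is c − i. Its variance is [(c + i) − (c − i)²]/n, which is at most 1/n. With 70 per arm, the standard error is at most 1/√70 = 0.120 and the 95% half-width at most 1.96 × 0.120 = 0.23. That would reveal gross recognition but not a slight imbalance.

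**The case against.** The strongest reply is that much of this rests on silence in a condensed article.

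- **The sham.** A reader might infer that the sham has no counterpart to the hand response. The text does not say so. It leaves the sham response undescribed, and technique may be set out in the full protocol. This stands: the point is that the description fails to support the claim, not that the sham is shown to be inadequate.
- **The stopping rule.** A reader might infer that needling continues until the hand reacts. The written criterion is the operator's sense of stagnation, and the patient's response is described as simultaneous. The same paragraph also aims at little or no pain, which sits awkwardly with the expected pain; those statements need reconciling. The response is still described as a feature of the real arm.
- **Protection.** It would be wrong to say that blinding is unprotected. Opaque sequential envelopes conceal allocation, the assessor and analysts are blinded, and the sham is matched on schedule and placed nearby. None of these covers what the patient perceives.
- **Missing check.** The absence of a blinding check from an article is not in itself an error, because the full protocol or analysis plan may contain one. This stands. The defect is an unqualified claim set against the article's own description and admission.
- **Recruitment material.** The Recruitment section mentions "obtaining necessary data, videos and pictures to help subjects understand the purpose and program of the trial". A reader might infer that these show the needling response. Nothing says so, and withholding an expected response from people deciding whether to consent would conflict with the same section's promise to explain advantages and disadvantages.
- **Magnitude.** The shift comes from no passage, and any assumed bias inflates error. This stands.

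**Conclusion.** The point holds in a limited form and should be acted on. The patient-blinding statement is untenable for the control arm and unsupported for acupuncture versus sham. The remedy offered, EMG, answers a different problem. The documents do not show that blinding will fail, and they do not allow the bias to be sized. The 8.7% to 39% range shows only what assumed shifts of 0.1 to 0.3 SD would do.

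The consequence is for interpretation. Without evidence on what patients believed, a difference between acupuncture and sham could not safely be read as an effect of the fascial point beyond that of being needled. The conclusion assumes that the response described for real needling usually occurs, and that patients know needling is what is being tested.

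**What to change.** 1. In Randomization, limit the statement on patients to acupuncture versus sham and word it as an aim. Say plainly that control patients are not blinded. Leave the assessor and analyst statements as they are.
2. Ask every needled patient once, right after the first session, which needling they think they had: real, sham or don't know. The early timing is meant to get the answer before benefit can drive it. The Background reports immediate relief in the 16 earlier cases, so early timing limits this influence but may not remove it.
3. Report the Bang index per arm with its confidence interval, and set down beforehand how it will be read. Call the contrast patient-blinded only if the index supports it.
4. If a guess is also taken at 4 weeks, keep it descriptive, since by then it partly reflects improvement. Do not test efficacy within guess categories: the guess arises after randomization, and conditioning on it can bias the comparison.
5. Do not remove the expected needling response from material shown before consent.

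The cost is one question at an existing contact, one table and a sentence of rewording. The downside is that the index may weaken the blinding claim. No needling procedure or clinical rule changes.
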